**Methods:**

Approximately 500 people who smoke cigarettes and access the Oklahoma Tobacco Helpline (OTH) will be randomized to receive standard OTH care (SC) or SC plus the novel OKquit smartphone app for smoking cessation (OKquit). All participants will use a smartphone app to complete study surveys (ie, baseline, 27 weekly surveys, brief daily check-ins, and 27-week follow-up). Upon completion of daily check-ins and weekly surveys, participants will receive either trivia type messages (SC) or messages that are tailored to current readiness to quit smoking and currently experienced lapse triggers (OKquit). In addition, those assigned to receive the OKquit app will have access to on-demand smoking cessation content (eg, quit tips, smoking cessation medication tips). It is hypothesized that participants assigned to OKquit will be more likely to achieve biochemically verified 7-day point prevalence abstinence than those assigned to SC at 27 weeks post enrollment. In addition, participants who use more OTH resources (eg, more cessation coaching sessions completed) or more OKquit resources (eg, access more quit tips) will have greater biochemically verified smoking cessation rates.

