### Procedure

Individuals who contact the OTH for smoking cessation services via the phone or web are asked whether they are interested in participating in a smoking cessation research study. Contact information for interested individuals is shared with OKquit research team members who then send a web-based Research Electronic Data Capture (REDCap) study screener link to these individuals. Those who complete the 5-minute REDCap screener and meet the initial study inclusion criteria then complete an enrollment call, which includes the informed consent process and a full study eligibility assessment. Those who enroll in the study receive instructions about how to download the Insight app onto their personal smartphone, and they are given 7 days to complete the 30-minute app-based baseline survey. Following completion of the baseline survey, research staff contact participants to randomize them into an intervention group. Randomization is stratified based on self-reported race and ethnicity (non-Hispanic White vs minoritized race and ethnicity), biological sex at birth (male vs female), and number of cigarettes smoked per day (20 vs ≥20). During the randomization call, all participants are asked to use the app to select a quit date within the next 21 days, are given instructions on how to access intervention content, and are instructed on how to complete the prompted daily check-ins and weekly surveys. Following randomization, participants interact with their assigned intervention for the 27-week study duration. Those who report abstinence from smoking during the 26th weekly survey are mailed a Bedfont carbon monoxide monitor that pairs with the Insight app by pressing the power button on the device, and they are asked to submit a breath sample for abstinence verification. Participants are also prompted to complete a 27-week follow-up assessment via the Insight app. The study flow is shown in Figure 1.

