More than 900 unique messages have been embedded into the OKquit app. Messages were taken from a message bank that was developed by this research team and have been evaluated by 6 tobacco experts [27]. Table 1 provides a summary of the various message types, the phases that messages are available or used, along with example messages. All messages begin with the participant’s first name. One message is delivered at the end of each check-in and weekly survey (up to 6 per day). Level 1 messages are presented during the Motivation phase. These messages aim to increase motivation and readiness to quit smoking. Level 2 messages are presented during the Pre–Quit Phase. These messages consist of content that aims to prepare the participants for their upcoming quit attempt. During the Post–Quit and Maintenance Phases, the participants receive personalized automated messages based upon their current risk of imminent smoking (a complete description of the lapse risk estimator is presented elsewhere [23]). When participant responses indicate a low degree of risk for smoking lapse during the Post–Quit Phase, level 3 messages are presented. Level 3 messages provide general coping strategies for lapse triggers that are commonly encountered early in quit attempts. When participants report that they smoked the day prior, or they indicate that they have more than 0% likelihood of smoking that day, level 4 messages are delivered. Level 4 messages provide suggestions on ways participants could cope with 1 of 4 currently experienced smoking lapse triggers (ie, easy access to cigarettes, high stress, high urge, or low motivation for cessation). Level 5 messages are delivered during the Maintenance Phase when the app algorithms indicate low risk for imminent lapse. Level 5 messages provide general advice on sustaining longer-term abstinence. If a participant reports multiple current triggers, 1 message is delivered in this order of priority: easy access to cigarettes, high stress, high urge, or low motivation for cessation. This order is based on findings from our previous research [19,20,23,24]. Specifically, variables that are better at indicating high risk for imminent lapse are given higher priority than variables that are less strongly linked with imminent lapse. When a participant initiates a Slip assessment, a level 6 message is presented at the completion of the assessment. Level 6 messages focus on encouraging participants to resume smoking abstinence.

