#### On-Demand Content

OKquit participants have access to various on-demand features available through the smartphone app home screen. The following features are accessible 24 hours a day for 27 study weeks and include (1) the “Quit Tips” button that offers a menu of treatment-related messages, relaxation exercises, and distraction videos, (2) the “Medication Tips” button that provides information about common smoking cessation medications (eg, nicotine gum, patch, and lozenges), such as medication use tips and common medication side effects, and (3) the “Additional Resources” button that provides helpful information and website links to useful resources (eg, COVID-19 tests, food, housing, and job placement resources). When a participant clicks the “Quit Tips” or “Medication Tips” buttons, a menu of options appears (see Figure 3 for menus and example messages).

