### Statistical Analysis

Descriptive statistics for continuous variables will include mean, SD, and quantiles, and categorical variables will be summarized as percentages and counts. We hypothesize that participants randomly assigned to the OKquit group will have significantly higher rates of biochemically verified 7-day point prevalence smoking abstinence than those assigned to SC at 27 weeks post randomization. We will use a chi-square test or Fisher exact test to compare the proportion of participants in the treatment conditions (ie, OKquit and SC) who are biochemically verified as abstinent (ie, iCO <7 ppm, and self-reports show no smoking in the past 7 days) 27 weeks after randomization. We will conduct the analysis using the intention-to-treat assumption wherein participants who are lost to follow-up or fail to complete the iCO evaluation will be classified as not abstinent. Prior to analyzing the data, we will examine the missing rate and patterns of missing data. If the missing rate is high, then we will explore sequential multiple imputation with at least 20 imputed data files as described by Raghunathan et al [47]. The analysis results from sequential multiple imputation data will be compared with those from the available data and intention-to-treat analyses. Based upon previous studies [48], we expect that 9% of those receiving the SC intervention will be biochemically confirmed abstinent at the 27-week post–quit follow-up, and based upon our pilot work, we expect that 18% of those receiving the OKquit treatment will be abstinent at the 27-week postquit follow-up visit [19,20]. With alpha values of .05 and 250 participants in each group, we have 84% power to detect a 9% difference in biochemically confirmed 7-day point prevalence abstinence at 27 weeks (ie, 45/250, 18% abstinent in the OKquit group vs 22/250, 9% abstinent in the SC group) by using Pearson chi-square test. In addition to the chi-square test or Fisher exact analysis, we will perform logistic regression analyses to determine whether the odds of abstinence vary by other baseline characteristics (eg, sex, race, and ethnicity). Finally, we will examine interactions between treatment condition and sex and race (separately) to identify potential differential effects on abstinence.

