We will examine secondary outcome measures from the collected data, including 30-day point prevalence abstinence, days to first lapse, and longest period of abstinence, which will be compared across treatment conditions. We will use the chi-square test or Fisher exact test and logistic regression models to examine 30-day point prevalence abstinence. For time to first lapse, Kaplan Meier and Cox regression modeling methods will be used. For the longest period of abstinence, *t* test or Wilcoxon rank sum test and linear regression methods will be used. Finally, we will use generalized linear mixed model regression analysis to compare abstinence rates between groups over time.

We hypothesize that OTH service engagement and use of OKquit intervention content will predict biochemically verified 7-day point prevalence smoking abstinence 27 weeks post randomization. Logistic regression models will be used to examine whether total number of OTH coaching sessions completed and OTH NRT shipments predict 27-week biochemically confirmed 7-day point prevalence abstinence. We will also examine whether the number and type of interactions with the OKquit app (eg, messages viewed) predict 27-week abstinence. Baseline characteristics such as race and sex will be considered as potential covariates during the modeling process.

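### The count of automated messages viewed shares non-response with the verified abstinence outcome, so it can predict abstinence even if the content has no effect

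*Protocol article*

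**What the plan says.** All references are to the protocol article.

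- **Hypothesis.** The Abstract (Methods) expects higher verified cessation among "participants who use more OTH resources (eg, more cessation coaching sessions completed) or more OKquit resources (eg, access more quit tips"). Statistical Analysis repeats the hypothesis for verified 7-day abstinence at 27 weeks.
- **Models.** For the helpline: "Logistic regression models will be used to examine whether total number of OTH coaching sessions completed and OTH NRT shipments predict" that outcome. For the app: "We will also examine whether the number and type of interactions with the OKquit app (eg, messages viewed) predict 27-week abstinence". The only adjustment named is for baseline characteristics, with race and sex as examples.
- **How messages arise.** Automated Messages: "One message is delivered at the end of each check-in and weekly survey (up to 6 per day"). The Check-Ins and Weekly Survey sections confirm that the message follows completion of the questions.
- **How abstinence is verified.** Procedure: "Those who report abstinence from smoking during the 26th weekly survey are mailed a Bedfont carbon monoxide monitor".
- **Missing outcomes.** Under the intention-to-treat rule in Statistical Analysis, "participants who are lost to follow-up or fail to complete the iCO evaluation will be classified as not abstinent".
- **Message level.** Phase and lapse risk determine it. For example: "Level 5 messages are delivered during the Maintenance Phase when the app algorithms indicate low risk for imminent lapse".
- **Interpretation.** Principal Results speaks of the *effects* of engagement and of app content on abstinence.

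**The concern.** Messages viewed is meant to measure exposure to content. For automated messages it also measures willingness to keep answering the app, and the same willingness is needed to be recorded as abstinent. A participant who stops responding collects few messages, does not answer the week-26 survey, is not sent a monitor and cannot be verified. If that participant is then scored as smoking, predictor and outcome fall together for a reason unrelated to content.

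A second problem arises if the *type* of interaction is taken to mean message level. Level is assigned from reported smoking and lapse risk, so it is partly an earlier reading of the outcome.

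This is a stated directional hypothesis. A significant positive slope could be published as evidence that using more app content helps people quit, when differential response and reverse causation could have produced it.

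**Working it through.** **1. The plan's own figure.** The engagement analysis has no stated figure. The primary power calculation reproduces. With 18% v 9%, 250 per arm, two-sided .05 and pooled proportion 0.135:

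- null SE = √(2 × 0.135 × 0.865 / 250) = 0.0306
- alternative SE = √((0.18 × 0.82 + 0.09 × 0.91) / 250) = 0.0303
- power = Φ((0.09 − 1.96 × 0.0306) / 0.0303) = 84.0%, against 84% stated.

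The point below does not affect it.

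**2. Why a null effect can look positive.** Let M be the automated-message count, A true abstinence, R completion of the steps needed for verification, and Y = A × R the recorded outcome when missing is scored as smoking. If content does nothing and A is independent of M and R, with P(A) = q, then

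P(Y = 1 | M) = q × P(R = 1 | M).

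Any dependence of R on M passes straight into Y. Among responders P(A = 1 | R = 1, M) = q, which is flat in M.

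**3. Size by simulation.** From the article: 250 OKquit participants, 18% recorded abstinent, and 27 × 7 = 189 morning check-ins. Assumed, because the article does not give them:

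- latent engagement u ~ N(0,1)
- M ~ Binomial(189, expit(0.4 + 1.2u))
- logit P(R = 1) = c + r·u, with c set to give the stated response
- q = 0.18 / response.

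Coupling r = 1 multiplies the odds of final response by e ≈ 2.7 per SD of engagement; r = 2 multiplies them by e² ≈ 7.4. Each setting has 2,000 runs of a logistic regression of Y on standardized M, rejecting at |z| > 1.96.

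| Response | q | r = 0: rejected | r = 1: rejected (OR per SD) | r = 2: rejected (OR per SD) |
|---|---|---|---|---|
| 90% | 0.200 | 5.0% | 8.8% (1.12) | 15.4% (1.20) |
| 80% | 0.225 | 5.1% | 23.3% (1.25) | 50.2% (1.42) |
| 70% | 0.257 | 4.5% | 45.2% (1.39) | 85.5% (1.69) |
| 60% | 0.300 | 5.3% | 70.3% (1.56) | 97.8% (2.04) |
| 50% | 0.360 | 5.9% | 87.3% (1.75) | 100% (2.51) |

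With r = 1 or 2, practically all rejections are positive. The same data analysed in responders only give 4.2% to 5.6% and an OR of 1.00 to 1.01. That clean result depends on A having been made independent of engagement.

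**4. Message level.** According to Procedure and Automated Messages:

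| Level | What leads to it | Expected association with abstinence |
|---|---|---|
| 5 | Maintenance Phase (entered after reporting no smoking in 7 days and high confidence) with low lapse risk | positive |
| 4 | smoked yesterday, or any stated likelihood of smoking today | negative |
| 6 | slip assessment | negative |
| 1 | Motivation Phase, after returning to smoking or ending the quit attempt | negative |

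A separate simulation used full response, no content effect and a weekly two-state smoking chain. Weekly quit/relapse probabilities were 0.05/0.22, 0.03/0.13 and 0.015/0.045, which left 18% to 20% abstinent at week 27. Level-5 count differed by final abstinence in 100% of 500 runs per setting, with about 26, 43 and 76 more messages in the abstinent. It simplifies by treating every abstinent week as seven level-5 messages, so the direction is informative and the counts are only illustrative.

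**5. Predictors outside the survey route.** On-Demand Content says of the tips and resource buttons: "The following features are accessible 24 hours a day for 27 study weeks". They need no survey. OTH Data says that coaching and nicotine replacement records come from the helpline. Neither count is a count of surveys. Both are totals with no stated cut-off, so relapse or success can change later use, and both are set against the same verified outcome.

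**The case against.** A reader might infer that the whole engagement hypothesis is circular and that a positive result is to be expected. The article does not support that, for five reasons.

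- **Other routes.** Messages viewed is only an example of app use. The Abstract's own example is opening quit tips, and coaching and nicotine replacement counts come from helpline records. This stands: the survey-count artefact is limited to prompted messages.
- **Type.** The text says type of interactions, not message level. It could mean tips, medication information or check-ins. Even if level were used, the signs would be mixed. This stands, so the level problem is conditional.
- **Missing data.** The missing-as-smoking rule is written for the treatment comparison. The same paragraph plans a look at missing-data patterns and, if missingness is high, multiple imputation set beside available-data results. Whether the rule or the safeguard extends to the engagement models is not said. This stands in part. The engagement models use the same verified outcome, the safeguard is conditional, and imputation would not cure reverse causation.
- **Size.** Response and coupling are not documented. Staff contact participants after missed weekly surveys, and payment covers surveys, follow-up and the breath sample but not check-ins, which may weaken the link between check-in count and final response. This stands: inflation is modest at 90% response and absent without coupling.
- **Status.** This is a non-randomized secondary analysis framed as prediction, and a condensed article may leave exposure windows to the full plan. That lowers the priority. It does not change what the stated predictor and outcome share, and Principal Results goes beyond prediction by speaking of effects.

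**Conclusion.** The point holds for automated messages. Their count is in effect a count of completed assessments, and the verified outcome depends on completing further assessments. If missing is scored as smoking, a positive association can appear with no content effect: about 9-15% of trials at 90% response, 23-50% at 80% and 87-100% at 50%, for the two assumed strengths of coupling, against about 5% with none. These ranges rest on assumed response, coupling and message-count distributions, and on the missing-as-smoking rule being carried over.

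Message level, if used, is set by reported smoking and lapse risk and should not be read as exposure. On-demand use and helpline counts do not have the survey-count artefact, but they share the outcome coding and are open to reverse causation. It would be wrong to conclude that a significant positive finding is assured, or that the randomized comparison is biased; neither follows. This should be fixed, but it does not threaten the primary result.

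**What to change.** Amend the engagement analysis as follows.

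1. Analyse on-demand use (quit tips, medication tips) separately from prompted messages, and do not use message level as a predictor.
2. Measure engagement, including coaching and nicotine replacement shipments, in a fixed early window. The first 4 weeks after randomization is one possibility; as the first quit date falls within 21 days, it leaves at least 28 − 21 = 7 days after that date. Relate this to week-27 abstinence, adjusting for baseline factors and smoking status at the landmark.
3. Report every engagement model with and without missing scored as smoking (available data or multiple imputation), whatever the missing rate. Responder-only fitting alone is not enough, since it leaves reverse causation in place.
4. Optionally, fit the same model to the trivia-message count in the standard-care arm as a negative control. That arm answers the same check-ins and surveys without cessation messages, so a similar slope there would argue against a content effect.
5. In Principal Results, replace *effects* of engagement with association wording.

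**Cost.** Wording and analysis time only. Late use is not counted. Landmark smoking status will be missing for those who skip that survey. The landmark for on-demand use assumes that access is time-stamped; the Measures overview states this only for check-ins and surveys, so it needs confirming. Helpline data carry dates.

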### Measures

#### Overview

The initial prescreener survey is completed via REDCap. The screener collects individual contact information and demographic information (eg, age, race, and biological sex at birth), average cigarettes smoked per day, and level of desire to quit smoking. The baseline assessment (30 minutes), weekly surveys (3-5 minutes each), daily check-ins (10-30 seconds), and 27-week follow-up assessment (20 minutes) are collected via the Insight app. See Table 2 for study assessments and administration schedule. For daily check-ins and weekly surveys, the phone rings and vibrates to prompt the participant to complete the assessment. If the participant does not respond after 5 prompts, the check-in/survey is automatically rescheduled up to 3 times 15 minutes later. Assessments collect information about several factors related to smoking, smoking lapse, and health. Participants are instructed to self-initiate “About to Slip” and “Already Slipped” assessments and to initiate the “Set New Quit Date” assessments when they want to set a new quit date. Each check-in and survey are date-, time-, and geolocation-stamped for future examination.

**Table 2 table2:** List and timeline of study measures.

Measure	Screener	Baseline	Follow-up
Screening Questionnaire	✓		
Phone Call Screener	✓		
Rapid Estimate of Adult Literacy in Medicine—SF (REALM) [25]	✓		
Tobacco History Questionnaire		✓	✓
Heaviness of Smoking Index [28]		✓	✓
Self-Efficacy Scale/Confidence [29]		✓	✓
Demographic/Background Information Questionnaire		✓	
MacArthur Scale of Subjective Social Status [30]		✓	✓
Overall Anxiety Severity and Impairment Scale (OASIS) [31]		✓	✓
Overall Depression Severity and Impairment Scale (ODSIS) [32]		✓	✓
The Patient Health Questionnaire-4 (PHQ-4) [33]		✓	✓
Financial Strain Questionnaire [34]		✓	
Perceived Stress Scale [35]		✓	✓
The Everyday Discrimination Scale (Brief version) [36]		✓	
The Pandemic Stress Index		✓	
Perceived Social Support Questionnaire [37]		✓	
Religious Participation [38,39]		✓	✓
Self-Rated health [40]		✓	✓
Health Related Quality of Life [41]		✓	✓
Alcohol Use Disorders Identification Test (AUDIT-C) [42]		✓	✓
Marijuana/Cannabis Use Behavior		✓	✓
BRFSS Inadequate Sleep [43]		✓	✓
Short Scale of Anxiety Sensitivity Index (SSASI) [44]		✓	✓
Cannabis Use Disorder Identification Test Short Form [45]		✓	✓
Weekly EMA^a^ items		✓	✓
Smoking Status items			✓
System Usability Scale [46]			✓
Treatment Quality and Satisfaction Survey			✓

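### Counting OKquit interactions with no early window, against an outcome that scores app leavers as not abstinent, can produce a use–abstinence link when the content has no effect

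*Protocol article*

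**What the plan says.** All references are to the protocol article.

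- **Exposure.** Statistical Analysis: "We will also examine whether the number and type of interactions with the OKquit app (eg, messages viewed) predict 27-week abstinence". The Abstract (Methods) words the hypothesis in terms of content taken up: those who use "more OKquit resources (eg, access more quit tips) will have greater biochemically verified smoking cessation rates".
- **How messages arise.** Automated Messages: "One message is delivered at the end of each check-in and weekly survey (up to 6 per day". Procedure has check-ins running for all 27 weeks, and On-Demand Content makes the extra features available for the same period.
- **Outcome.** Under Measures, Overview, the "27-week follow-up assessment (20 minutes) are collected via the Insight app". Procedure adds that the carbon monoxide monitor is mailed to those who report abstinence in the app's 26th weekly survey, and that it pairs with the app.
- **Missing outcomes.** Statistical Analysis: "participants who are lost to follow-up or fail to complete the iCO evaluation will be classified as not abstinent". If missingness is high, multiple imputation is to be explored and compared with the available-data and intention-to-treat results.
- **Adjustment.** The engagement models name baseline characteristics, with race and sex as examples.
- **Interpretation.** Principal Results, in the Discussion, speaks of effects of engagement on abstinence.

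**The concern.** Exposure and outcome share a cause that is neither smoking nor content: staying in the app. Someone who stops using it at week 8 collects few messages. That person also never completes the 26th weekly survey, is not sent a monitor and gives no breath sample, and so is scored as not abstinent whatever their true smoking status. Baseline covariates cannot remove a dependence that arises after randomization.

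There is a second route. If people who relapse tend to leave the app, low use is a consequence of smoking rather than a cause of it.

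At stake is the OKquit-use half of the engagement hypothesis. A positive coefficient could be published as a dose–response for the app when it partly or wholly reflects retention.

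**Working it through.** **1. The plan's own figure.** The article states: "With alpha values of .05 and 250 participants in each group, we have 84% power to detect a 9% difference", with "45/250, 18% abstinent in the OKquit group vs 22/250, 9% abstinent in the SC group". The mean rate is (0.18 + 0.09)/2 = 0.135.

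z = [0.09·√250 − 1.96·√(2·0.135·0.865)] / √(0.18·0.82 + 0.09·0.91) = (1.4230 − 0.9472)/0.4791 = 0.993

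This gives power of 83.97%, so the 84% is reproduced with a two-sided test. It is not in dispute. It supplies the two planning inputs used below: 250 participants in the OKquit arm, 18% of them verified abstinent. The article gives no figure for the engagement analysis.

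**2. The mechanism by hand.** Assume that a share d leaves the app for good at a time spread evenly over weeks 0–26. Leavers then have on average 13 weeks in which to collect messages, and stayers have 27. Under the scoring rule all 45 verified abstainers (18% of 250) must be stayers.

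| Assumed d | Leavers, scored abstinent | Stayers, scored abstinent |
|---|---|---|
| 10% | 0 of 25 | 45/225 = 20.0% |
| 20% | 0 of 50 | 45/200 = 22.5% |
| 30% | 0 of 75 | 45/175 = 25.7% |
| 40% | 0 of 100 | 45/150 = 30.0% |

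The group with about half the exposure time has a success rate of zero by rule.

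**3. Size under a null effect.** The logistic regression of scored abstinence on the standardized 27-week message count was simulated with true abstinence independent of use. Assumptions that are not in the article: permanent drop-out at a uniform time, a gamma-distributed personal message rate, and no link between that rate and drop-out.

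| Drop-out | Two-sided rejection (nominal 5%), 10 messages/week, CV 1.0 / 0.5 | Significant positive association (nominal 2.5%), 14 messages/week, CV 0.5 | Median OR per SD, 14 messages/week |
|---|---|---|---|
| 10% | 6% / 12% | 10% | 1.13 |
| 20% | 15% / 30% | 33% | 1.27 |
| 30% | 20% / 59% | 56% | 1.39 |
| 40% | 40% / 85% | 83% | 1.55 |

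The first set used 600 trials per scenario (Monte Carlo standard error at most √(0.25/600) = 2 points), the second 1,500. A repeat of the two-sided calculation gave 6–7%, 13–32%, 22–54% and 41–82%. Taken together, the two-sided ranges are 6–12%, 13–32%, 20–59% and 40–85%. In the second set, at 30% drop-out, scored abstinence was 22.7% above the median of use and 13.4% at or below it, with no content effect.

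**4. Does handling the missing outcomes suffice?** With drop-out unrelated to smoking, a complete-case analysis brought positive findings back to 1.7–3.1% (nominal 2.5%). With every outcome known but relapsers at 2–3 times the odds of leaving the app, and drop-out of 20–30%, the 27-week count still gave 9–20%. Imputing outcomes therefore deals with the first route but not the second.

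**5. Does an early window suffice?** Counting messages in weeks 1–4 among those still using the app at week 4 gave 2.4–3.3% positive findings (nominal 2.5%), with a median OR of 0.99–1.01, including in the relapse-linked scenarios with outcomes known. Across all the two-sided runs, early-window counts rejected in roughly 3–8%.

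**The case against.** Several counter-arguments have force.

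- **The window is not stated.** The article never says that use is summed over 27 weeks. This stands. It is the natural reading, because no narrower window is given, app content runs for 27 weeks, and the parallel helpline measure is a total. A full protocol or analysis plan may be narrower.
- **Messages viewed is only an example and is not purely a completion count.** This also stands. The Quit Tips menu contains messages, slip assessments trigger level 6 messages, and the plan allows counts by type. Slip messages rise with lapsing and would push the association the other way. The bias described here applies to totals dominated by check-in and survey messages.
- **Missing data are addressed.** The imputation and available-data comparison is written around the between-arm test, but so is the missing-equals-not-abstinent rule. If one carries over to the engagement model, the other may too. It is conditional on an undefined high missing rate, and step 4 shows that it would remove only part of the problem.
- **Retention may be good.** Staff contact after missed weekly surveys, $5 per survey and $50 for follow-up all work against permanent exit, and the simulations allow no return. At 10% drop-out the inflation is modest.
- **Prediction is not causation.** The analysis section does speak of prediction, but the Discussion speaks of effects.

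A reader might infer that the hypothesis is bound to be confirmed. The figures do not support that: at 20% drop-out, at least about two-thirds of null trials (100 − 32 = 68%) show no significant association.

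**Conclusion.** The concern holds in limited form. The exposure example, the outcome rule and the adjustment that the article names can together yield a positive use–abstinence association with no content effect. This is more than missing detail, because each element is stated and the combination is what fails. Its size ranges from slight (6–12% against a nominal 5%) at 10% drop-out to severe (40–85%) at 40%. It depends on drop-out, message rates and use patterns that the article does not report, and on use being counted over the whole study.

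It does not reach the randomized comparison, which does not use the interaction count. Nor does it cover the coaching and nicotine replacement models, whose exposures come from helpline records rather than app counts. It would be wrong to extend it to the engagement hypothesis as a whole.

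**What to change.** Amend the engagement paragraph before the data are analysed:

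1. Count OKquit use in a fixed early window, for example the first 28 days after randomization, among participants still using the app at its end. Because the first quit date is set within 21 days, this window runs at least 7 days past it unless the date is reset. Keep on-demand content (Quit Tips, Medication Tips, Additional Resources) and automatically delivered messages as separate exposures. The article treats both as intervention content, so neither should be dropped.
2. Report the model with missing scored as not abstinent and with observed or multiply imputed outcomes. Both are needed: if light early users also leave more often later, the scoring rule would still bias an early-window count.
3. Show results with and without adjustment for smoking status at the end of the window. That status may be a mediator, so the adjusted result should not stand alone.
4. As a supporting check, fit the same model to trivia messages viewed in the standard-care arm. A similar slope there would point to retention rather than content.
5. Report an association, and align the Discussion's wording on effects with that.

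Only the early-window message count was simulated. Separate on-demand exposures, the adjustment in item 3 and the standard-care check rest on reasoning.

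The cost is plan wording and a few extra models; check-ins and surveys are already time-stamped. Use after the window is not counted, and slightly fewer participants are analysed.
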